## Methods

### Study design and data collection

We use a two part-study design, combining a randomized controlled trial (RCT) and a longitudinal follow-up design.

The main study is a randomized control superiority trial, comparing the intervention group (IG) with a waiting-list control group (CG). For legal reasons, any insurant of the statutory German Pension Insurance (GPI) whose application for medical rehabilitation was approved by the GPI will receive a rehabilitative intervention. Therefore, it is not possible to use an entirely untreated CG, but a waiting-list CG can be realized. After inpatient rehabilitation in the Bad Reichenhall Clinic has been approved by the GPI, patients receive a letter informing about the study and screening for their eligibility. If no response is received within 14 days, a reminder will be sent to the patients. If patients meet the inclusion criteria, they are asked to participate. After consent has been obtained, participants will be randomized to the IG or CG. In the IG, participants will start inpatient rehabilitation within 4 weeks after randomization. Data will be assessed at randomization (T0), at the beginning (T1), the end (T2), and three months after inpatient rehabilitation (T3). The CG will start inpatient rehabilitation five months (i.e. 20 weeks) after randomization. CG data will be assessed at randomization (T0), at four weeks (T1), at seven weeks (T2) and at 20 weeks (T3, beginning of inpatient rehabilitation) after randomization. The crucial reference intervals for the primary research questions are T0 to T2 and T0 to T3 for both IG and the CG. Since CG starts PR 19 to 20 weeks after T0, which is 3 months after the discharge time-point of IG, it will be possible to compare the results of IG with those of the (still) untreated CG during these initial 19 to 20 weeks. However, it may be possible that for the CG, arrival at the rehabilitation clinic (at T3) already has an effect on several outcome parameters. To estimate this “arrival effect”, an additional measurement time point (T3a) for the CG at 10 (+/-3) days before T3 has been included.

The second part of the study is a longitudinal cohort study. In addition to the data collected in the first part of the study (RCT), data at 6, 9 and 12 months after inpatient rehabilitation in the IG and data at the end of and at 3, 6, 9 and 12 months after inpatient rehabilitation in the CG will be collected. Longitudinal data from both groups will be combined to one sample. Fig. 1 illustrates the study design. Note that measurement time points of the IG and CG have a parallel timing only from T0 to T3. Participants not returning the postal questionnaires on time will be reminded by phone. If necessary, questionnaires will be sent again by mail to the patient.

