**Methods:**

The EPRA study is a single-center randomized controlled waiting-list trial in the Bad Reichenhall Clinic. Inclusion criteria include a referral diagnosis for uncontrolled asthma, no cognitive impairment and no very severe co-morbidities that indicate significantly greater illness morbidity than asthma alone. In the intervention group (IG), participants will start PR within 4 weeks after randomization; participants of the control group (CG) will start PR 20 weeks after randomization. Data will be assessed at randomization (T0), after 4 weeks (T1; IG: begin of PR), 7 weeks (T2; IG: end of PR), and 20 weeks (T3, CG: begin of PR). The primary outcome is asthma control at T2/T3. Secondary outcomes are health-related quality of life, functional exercise capacity, dyspnea, anxiety, depression, subjective self-management skills, illness perceptions, sick leave and subjective work ability. Outcomes will be analyzed with analysis of covariance, including baseline values of the respective outcomes as covariates. Healthcare costs will be analyzed with a gamma model with a log-link.

A longitudinal follow-up study will generate additional data at 3/6/9/12 months after PR for both IG and CG. Latent change models will be used to analyze the course of the primary and secondary outcomes. Annual cost differences before and after rehabilitation will be compared by paired t-test.

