### Intervention

As shown in Fig. 1, both groups receive a 3-week PR that meets the structural requirements of German healthcare insurance providers [31, 32]. The PR is carried out by a multi-professional team (physicians, psychologists, physiotherapists, sports scientists, social workers, nutritional consultants) and will be tailored individually to each patient’s needs. The rehabilitation program will be reviewed at least once a week as part of the doctor’s weekly rehabilitation ward round.

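### Intervention-group visits follow rehabilitation dates while control-group visits follow fixed weeks, so the stated parallel timing to T3 is not guaranteed: the intervention group may be measured 0 to 4 weeks earlier

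*Protocol article*

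**What the plan says.** All references are to the protocol article.

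- **IG start** (Study design and data collection): "In the IG, participants will start inpatient rehabilitation within 4 weeks after randomization". No earliest date is given, and the abstract repeats the same upper limit.
- **IG visits** (same section): "Data will be assessed at randomization (T0), at the beginning (T1), the end (T2), and three months after inpatient rehabilitation (T3").
- **CG visits** (same section): "at four weeks (T1), at seven weeks (T2) and at 20 weeks (T3, beginning of inpatient rehabilitation) after randomization".
- **Abstract, Methods**, one schedule for both arms: "Data will be assessed at randomization (T0), after 4 weeks (T1; IG: begin of PR"), then "7 weeks (T2; IG: end of PR), and 20 weeks (T3, CG: begin of PR").
- **Alignment** (Study design and data collection): the CG's start at weeks 19 to 20 is equated with three months after IG discharge. The section closes by saying that the "measurement time points of the IG and CG have a parallel timing only from T0 to T3".
- **Programme length** (Intervention): "both groups receive a 3-week PR".
- **Analysis** (Statistical methods): T2 and T3 outcomes are compared by ANCOVA with treatment group and the baseline value of the outcome. The design section names T0 to T2 and T0 to T3 as the key intervals for the primary questions.

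**The concern.** The two arms run on different clocks: dates of rehabilitation in the IG, weeks since randomization in the CG. They agree only if an IG patient begins at week 4. Anyone admitted earlier has T2 and T3 sooner after randomization than the CG patients with whom they are compared.

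This touches the primary contrast. Entry requires an Asthma Control Test (ACT) score below 20 at T0, so some untreated change after T0 is plausible, for example regression to the mean. If such change is still under way between weeks 16 and 20, arms measured at different elapsed times carry different amounts of it. Adjustment for the T0 value cannot remove that, because the difference lies in when the outcome is taken. The target effect is small (d = 0.3), so even a modest shift could matter.

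**Working it through.** **Inputs from the article.** IG start s between 0 and 4 weeks after randomization; programme 3 weeks; CG visits at weeks 4, 7 and 20; design effect d = 0.3, alpha 0.05, power 0.8, 352 analysed and 504 recruited. Three months is taken as 13 weeks, the article's own spacing of T2 and T3 (20 − 7 = 13).

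**The plan's own figures.** A start at week 4 gives 4 + 3 = 7 and 7 + 13 = 20, so the 4/7/20 schedule is coherent for that start. The 19-to-20-week sentence implies s = 19 − 16 = 3 to s = 20 − 16 = 4. A two-sample t-test (two-sided and 1:1, both assumed) needs 175.4, so 176 per arm, or 352. Dividing, 352 / 0.7 = 502.9, which gives 503, or 504 when made even. The sample size reproduces and does not depend on this point.

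**IG visits by start week.** T1 = s, T2 = s + 3, T3 = s + 16; gap = CG week minus IG week.

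| IG start (week) | T1 | T2 | T3 | Gap to CG (weeks) |
|---|---|---|---|---|
| 4 | 4 | 7 | 20 | 0 |
| 3 | 3 | 6 | 19 | 1 |
| 2 | 2 | 5 | 18 | 2 |
| 1 | 1 | 4 | 17 | 3 |
| near 0 | 0 | 3 | 16 | about 4 |

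The gap is the same at T1, T2 and T3 and has one sign. Under the 19-to-20-week alignment only the first two rows apply.

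**ACT recall.** The ACT covers the last 4 weeks. CG recall at T3 is weeks 16 to 20. A start at week 3 gives IG recall of weeks 15 to 19 (3 weeks shared); a start at week 1 gives weeks 13 to 17 (1 week shared).

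**Possible size of bias.** Bias = untreated drift per week × gap. The article gives no drift, so 0.005 to 0.03 SD per week is assumed for illustration. Power is for 176 per arm if the drift is an improvement, against 0.80 with no gap.

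| Gap | Bias (SD) | Share of d = 0.3 | Power if diluted |
|---|---|---|---|
| 1 week | 0.005 to 0.03 | 2% to 10% | 0.790 to 0.717 |
| 2 weeks | 0.01 to 0.06 | 3% to 20% | 0.777 to 0.615 |
| 4 weeks | 0.02 to 0.12 | 7% to 40% | 0.748 to 0.393 |

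The gap here is the average over IG patients. A 2-week average would arise if starts were spread evenly over weeks 0 to 4, which is also an assumption. The 4-week row is the limit in which every IG patient begins at once. If the drift is a worsening, the IG effect is inflated by the same amounts.

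**The case against.** The strongest reply is that the article does give a common schedule. The abstract sets weeks 4, 7 and 20 for both arms, and the design section ties the CG's start at weeks 19 to 20 to three months after IG discharge. Read together, these imply IG starts at about week 3 to 4 and a gap of 0 to 1 week. A start at week 0 would also merge T0 and T1, which Table 1 lists as separate ACT assessments. This stands: the intended gap is probably small. But the start rule, as worded in both places, does not enforce it.

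Second, the effect of a gap is not shown. Regression to the mean need not grow with elapsed time, and weeks 18 and 20 may hardly differ. If untreated patients improve, the later-measured CG gains more, which works against the IG and is conservative for a superiority trial. This stands as well, and it is why the bias is given only as a range under an assumed drift.

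Third, the primary question concerns asthma control three months after rehabilitation, so tying IG T3 to discharge fits the stated aim. That is fair, but the article also claims parallel timing, and for early starters both cannot hold.

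Fourth, visit windows and admission scheduling may be in the full protocol, and Fig. 1 is not shown. Their absence is not the point here. The point is that timing statements printed in the article do not agree.

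A reader might go further and infer that the parallel timing fails, or that the comparison with an untreated CG is lost for early starters. The article does not support either reading. No start dates are given, and at the extreme IG T3 falls at weeks 16 to 20, while the CG begins rehabilitation at about week 20. The CG is therefore untreated throughout the comparison.

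**Conclusion.** The point holds in a limited form. The upper-limit start rule, with IG visits tied to rehabilitation and CG visits tied to randomization, does not guarantee either the 4/7/20 schedule or the parallel timing. The mismatch at T2 and T3 lies between 0 and 4 weeks (0 to 1 week if the 19-to-20-week alignment is kept), always with the IG measured earlier, and the planned ANCOVA has no term for it.

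These limits rest on a 3-week programme and 13 weeks for three months. The size and direction of any bias are unknown: the SD and power figures above depend on an assumed drift, and the average gap depends on start dates that are not given. The randomized contrast with its common T0 is not invalidated. This is an avoidable, one-directional timing difference in the primary comparison that can be removed cheaply at T3.

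**What to change.** 1. **Reconcile the text.** Bring the start rule in the abstract and design section into line with the 4/7/20 schedule and the parallel-timing statement. Which start rule applies is for the sponsor to settle.
2. **Anchor the primary assessment.** Send the T3 ACT questionnaire to every IG patient at week 20 after randomization, with the same window as the CG. This follows the abstract's own schedule.
3. **Record days since randomization** for T2 and T3 in both arms, and add a sensitivity analysis by elapsed time. T2 needs this because it is by definition the end of rehabilitation, so its timing cannot be fully aligned. The CG's repeated untreated ACT values (T0, T1, T2, T3a) can inform the drift.

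Moving CG dates to match IG starts is not a good alternative: CG patients are not paired with IG patients, and CG T3 would be detached from admission, where the article places it.

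**Cost.** Wording, the posting date of a questionnaire that IG patients already complete after discharge, one date field and one extra analysis. The downside is that early starters are assessed later relative to discharge. For a start near week 0, week 20 is 20 − 3 = 17 weeks after discharge rather than 13, so up to about 4 weeks beyond three months. The description of T3 should say so.

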**Fig. 1 Fig1:**
[figure not shown]
Study design and measurement occasions; PR: pulmonary rehabilitation; M: months; W: weeks; not shadowed: data for randomized control trial; grey shadowed: data used only in the longitudinal study

### Patient selection

Patients are eligible for the study if they are approved for PR, have a physician diagnosis of asthma (ICD-10: J45) at T0 and have uncontrolled asthma based on an Asthma Control Test (ACT) <20 [1, 29, 30]. Patients will be excluded if they have cognitive impairment, inadequate German language ability, or severe concomitant diseases that might mask the results of asthma rehabilitation (for example cancer and severe cardiac/orthopedic or psychiatric comorbidities). The initial diagnosis of asthma will be confirmed by a pulmonologist at admission to inpatient rehabilitation. If the initial diagnosis cannot be confirmed, the patient will be excluded from the study.

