### Randomization

Participants will be recruited consecutively. All patients meeting the inclusion criteria and providing informed consent are randomly assigned to the IG or CG by a study nurse at the time of their PR approval. Randomization will be stratified according to age. The randomization list (with computer-generated random numbers) is created by the Department of Medical Psychology and Psychotherapy, Medical Sociology and Rehabilitation Sciences at the University of Würzburg (concealed allocation).

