### Statistical methods

Primary and secondary outcomes will be analyzed according to the intention to treat approach [56]. All randomized patients will be included in the analysis. Missing data fulfilling the assumption of missing (completely) at random will be imputed using multiple imputation procedures [57]. In addition, because it may be possible that some patients will not start with the inpatient rehabilitation or decide to drop-out of the study, we will also analyze results based on a “per protocol” approach [58, 59] including only patients remaining in the study until T3.

The analysis of the primary and secondary outcomes at T2/T3 will use analysis of covariance (ANCOVA) with treatment group as a fixed effect and baseline value of the respective outcome as a covariable. Adjusted mean differences and confidence intervals will be reported. In addition, moderating effects [60] of the following baseline variables on the primary outcome will be analyzed: ACT, gender, age, quality of life (assessed via SGRQ Total Score), anxiety (assessed using GAD-7) and depression (assessed using PHQ-7). For all models, statistical model assumptions (linearity, homoscedasticity, normality of residuals) will be tested. If model assumptions are violated, appropriate analysis methods (e.g. robust regression, log-transformation) will be used.

Latent change models will be used for exploratory analyses of the course of the primary and the secondary outcomes in the follow-up longitudinal study [61, 62].

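### Excluding patients whose asthma is not confirmed at admission acts after randomization, by week 4 in one arm and about week 20 in the other, and is not reconciled with the all-randomized analysis

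*Protocol article*

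**What the plan says.** Under Randomization, the protocol article says that eligible, consenting patients "are randomly assigned to the IG or CG by a study nurse at the time of their PR approval". Under Patient selection, it places the diagnostic check later: "The initial diagnosis of asthma will be confirmed by a pulmonologist at admission to inpatient rehabilitation". The consequence of a negative check follows: "If the initial diagnosis cannot be confirmed, the patient will be excluded from the study".

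Study design and data collection fixes when admission happens in each arm. For the IG: "In the IG, participants will start inpatient rehabilitation within 4 weeks after randomization". For the CG: "The CG will start inpatient rehabilitation five months (i.e. 20 weeks) after randomization". The same section also gives 19 to 20 weeks for the CG, and CG admission coincides with T3.

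Under Statistical methods: "Primary and secondary outcomes will be analyzed according to the intention to treat approach", and "All randomized patients will be included in the analysis". Data missing (completely) at random are to be multiply imputed. No exception is made for patients whose diagnosis is not confirmed.

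**The concern.** Removing ineligible patients after randomization can be harmless if the finding is unrelated to treatment and the rule reaches both arms at the same point and with the same completeness. Here it does not. The check is tied to admission, and the time of admission is exactly what randomization assigns.

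Two things are at stake. First, the text does not settle whether an unconfirmed patient belongs to the primary analysis set. Left open, that could be decided after outcomes are known. Second, if these patients are dropped, the compared groups have been filtered at different times and after different attrition, which weakens the protection that randomization gives the primary contrast.

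**Working it through.** **Sample size, to see whether it is affected.** The inputs from Sample size are d = 0.3, alpha 0.05, power 0.80 and 30% drop-out; 1:1 allocation and a two-sided test are assumed. The two-sample t-test needs 175.4, so 176 per arm and 352 in total, as stated. Drop-out gives 352 / 0.7 = 502.9, so 503, or 504 for equal arms, as stated. Keeping every randomized patient in the analysis changes neither figure.

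**What the rule does in each arm** (Study design and data collection; Patient selection; Table 1):

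| | IG | CG |
|---|---|---|
| Check after randomization | at most 4 weeks (T1) | 19 to 20 weeks (T3) |
| Position | before treatment, before T2 and T3 | after T2 and T3a, at T3 |
| ACT data of an excluded patient | no T2, no T3 | T0 to T2 and T3a already due |
| Patient lost between weeks 4 and 20 | normally already checked | never checked |

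The gap between the checks is at least 19 − 4 = 15 to 20 − 4 = 16 weeks.

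**Two readings of the exclusion sentence.**

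- *Excluded from the analysis as well.* This contradicts the statement that all randomized patients are analysed, and the filter differs by arm.
- *Excluded from follow-up only, then imputed.* The all-randomized statement is kept. However, every unconfirmed IG patient then lacks T2 and T3, so the IG imputation can draw only on patients not found to be unconfirmed. In the CG, T2 and T3a values of unconfirmed patients are observed. The information lost still differs by arm.

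**Illustrative size under the first reading.** The documents give none of these inputs, so all are assumptions: unconfirmed share p = 5, 10 or 15%; share checked c = 0.9 in the IG and 0.7 in the CG; unconfirmed patients differ in outcome by 0.3 to 0.5 SD; reaching the check does not depend on the diagnosis. The unconfirmed share left in an arm is s = p(1 − c) / (1 − pc), and the bias is (s in CG − s in IG) × SD difference.

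| p | s, IG | s, CG | Difference | Bias (SD) |
|---|---|---|---|---|
| 5% | 0.005/0.955 = 0.5% | 0.015/0.965 = 1.6% | 1.0 points | 0.003 to 0.005 |
| 10% | 0.010/0.910 = 1.1% | 0.030/0.930 = 3.2% | 2.1 points | 0.006 to 0.011 |
| 15% | 0.015/0.865 = 1.7% | 0.045/0.895 = 5.0% | 3.3 points | 0.010 to 0.017 |

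As an extreme bound, let every IG patient and no CG patient be checked. The bias is then p × SD difference: 0.05 × 0.3 = 0.015 to 0.10 × 0.5 = 0.05 SD for p of 5 to 10%, and up to 0.15 × 0.5 = 0.075 SD at 15%.

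**The case against.** The strongest reply is that the two statements govern different things: one is about taking part in the study, the other about the analysis set. A patient can leave follow-up and still be analysed with baseline data and imputed values. That stands, so a reader who infers that the two sentences cannot both be followed goes too far. What remains is that the article does not say which reading holds, and that the arm-dependent loss of data survives the milder one.

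A reader might also infer that the CG is judged by a different standard. The documents do not support this. Rule, clinic and type of assessor are the same, and under Blinding those delivering treatment do not know study participation or arm, which probably covers the admitting pulmonologist. Blinding limits arm-driven judgement, but it cannot equalise when, or whether, a patient is checked.

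A loss of power is a third tempting inference. It would need an unconfirmed rate that the article does not give, and it vanishes if these exclusions already sit within the 30% drop-out.

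Finally, the per-protocol set, "including only patients remaining in the study until T3", might be read as keeping IG patients who never start rehabilitation. That depends on how T3 is understood for them. Study design and data collection defines IG T3 as three months after rehabilitation, which a non-starter never reaches, while the Abstract counts weeks from randomization. It is a separate question and no part of this point.

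On the illustration, the objection that its inputs are unsourced is fair. In particular, 70% checked in the CG borrows the drop-out rate as a stand-in for not being admitted. The article does not equate the two, and it says that every approved insurant receives rehabilitation.

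**Conclusion.** The point holds as a conflict to be reconciled, not as a demonstrated large bias. A rule applied after randomization takes out patients, or at least their later outcomes, at a time and with a probability that depend on the assigned arm, and it is not squared with the intention-to-treat statement.

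Under the stated assumptions the bias is about 0.003 to 0.017 SD, at most 0.017 / 0.3 = 6% of the planned effect. The extreme bound reaches 0.05 SD (17%) at 10% unconfirmed and 0.075 SD (25%) at 15%. Its direction is unknown. It is therefore likely to be small unless unconfirmed diagnoses are common. The case for a change rests on fixing the primary analysis population before outcomes are seen.

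**What to change.** - Replace the exclusion sentence under Patient selection: randomized patients whose asthma is not confirmed at admission continue to receive the study questionnaires and stay in the primary intention-to-treat analysis.
- Report, by arm, how many patients were unconfirmed and how many were never checked.
- Present any analysis restricted to confirmed asthma only as a supportive sensitivity analysis. State the caveat that the check is reached at different times and after different attrition in the two arms, so this restriction carries the same arm-dependent selection.

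The cost is a change of wording and a few more questionnaires. The downside is slight dilution of the intention-to-treat effect by patients without asthma, whose share is equal in expectation between the arms. The sample size needs no change.
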